### Sample size and justification

The primary outcome of this study will be the QoR-15 score at 24 h postoperatively. The established minimum clinically important difference in QoR-15 is 8.0 and the mean SD of QoR-15 scores after major spinal surgery is in the order of 14 [range of QoR score is 1–150]. Therefore, assuming type I error = 0.05 and type II error = 0.2 (80% power to detect this difference), then *n* = 25 patients will be required in each group. To accommodate for participants who may withdraw from the study, we will aim to recruit *n* = 26 patients to each study arm.

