**Methods:**

We are conducting a prospective, randomised, double-blind trial in two hospitals in the Republic of Ireland. The sample size will be 50 patients (25 in the intervention group and 25 in the control group). Randomisation will be done using computer-generated concealed envelopes. Both patients and investigators collecting outcome data will be masked to group allocation. Participants will be male or female, aged 18 years and over, capable of providing informed consent and ASA grade I–IV. Patients scheduled to undergo posterior approach thoraco-lumbar decompression surgery involving 2 or more levels will be recruited to the study. Participants randomised to the intervention arm of the study will receive bilateral ultrasound-guided ESP block totalling 40 ml 0.25% levo-bupivcaine (20 ml each side), post induction of general anaesthesia and before surgical incision. The control group will not receive an ESP block. Both groups will receive the same standardised analgesic protocol both intra- and postoperatively. The primary outcome will be the quality of recovery at 24 h postoperatively as determined by the QoR-15 score. This score is determined by a questionnaire which measures patient responses to 15 subjective parameters, each response graded on a scale from 0 to 10. The maximum score achievable is 150 with a potential minimum score of 0. Higher scores indicate a higher quality of recovery experience.

Secondary outcomes will include area under the curve (AUC) of VRS pain versus time at rest and on movement up to 24 h postoperatively, 24 h opioid consumption, time to first analgesia in recovery, length of stay (LOS), incidence and severity of postoperative complications as measured by the Comprehensive Complication Index (CCI) score.

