### Statistical considerations

Data will be inspected and tested for distribution according to the Kolmogorov-Smirnov test. Normally distributed data will be compared between study arms using the unpaired *t* test, whereas non-normally distributed data will be compared using the Mann-Whitney *U* test. All data will be summarised as mean + SD or median (25–75% range) as appropriate.

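### The stated inputs require about 50 patients per arm, not 25: at 25 per arm, power for an 8-point QoR-15 difference is about 51%, not 80%

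*Protocol article*

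**What the plan says.** Under Sample size and justification, the protocol article gives all the inputs in one paragraph:

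- Endpoint: "The primary outcome of this study will be the QoR-15 score at 24 h postoperatively".
- Difference to detect: "The established minimum clinically important difference in QoR-15 is 8.0".
- Variability: "the mean SD of QoR-15 scores after major spinal surgery is in the order of 14".
- Error rates: "assuming type I error = 0.05 and type II error = 0.2 (80% power to detect this difference").
- Conclusion: "n* = 25 patients will be required in each group", with 26 per arm to be recruited to allow for withdrawals.

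The Abstract (Methods) gives the size as "The sample size will be 50 patients (25 in the intervention group and 25 in the control group"), and the end of the Background repeats the total of 50. Statistical considerations names the between-arm comparison: "Normally distributed data will be compared between study arms using the unpaired *t* test", with the Mann-Whitney U test otherwise. The Discussion says that no preoperative QoR-15 will be taken, so adjustment for a baseline score cannot reduce the variance. Whether the test is one- or two-sided is not stated.

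**The concern.** A difference of 8 with an SD of 14 is a standardised effect of 0.57. Two parallel groups of 25 are too small to detect an effect of that size with 80% power. The paragraph presents 25 as following from its own inputs, and this is the only justification given for the size of the trial.

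If the arithmetic is wrong, the trial lacks the power it claims for its primary question. The practical risk lies in reading the result: a null finding reported beside a claim of 80% power would look like evidence against a worthwhile benefit, when the trial had about an even chance of missing one.

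**Working it through.** **Inputs** (Sample size and justification): difference 8.0; SD 14; type I error 0.05; power 0.80; equal arms. A two-sided test is assumed because sidedness is not stated.

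**Step 1. Required number, normal approximation.**
n per arm = 2 × (1.960 + 0.842)² × (SD/difference)² = 2 × (1.960 + 0.842)² × (14/8)² = 48.07, rounded up to **49 per arm (98 in total)**.

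**Step 2. Required number, two-sample t test.**
With standardised effect 8/14 = 0.571, the noncentral t calculation gives 49.05, rounded up to **50 per arm (100 in total)**. Power at 50 per arm is 80.8%.

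**Step 3. Can the plan's figure of 25 be reproduced?** The article shows no formula. No two-group calculation from these inputs gives 25:

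| Variant | Required per arm |
|---|---|
| Two-sided, normal approximation | 49 |
| Two-sided t test | 50 |
| One-sided 0.05, normal approximation | 38 |
| One-sided 0.05 t test | 39 (38.6) |
| Two-sided Mann-Whitney, relative efficiency 0.955 (normal data) | 52 (49.05/0.955 = 51.4) |
| Two-sided Mann-Whitney, relative efficiency 0.864 (lower bound) | 57 (49.05/0.864 = 56.8) |

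Leaving out the factor of 2, as in a one-sample or paired calculation, gives (1.960 + 0.842)² × (14/8)² = 24.04, which rounds up to 25. Using the per-arm requirement of 49 to 50 as the total and halving it also lands at 25. Either slip could explain the figure, but that is inference, and neither calculation fits a parallel-group design.

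**Step 4. Power with the stated numbers** (t test, difference 8, SD 14):

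| Per arm | Two-sided | One-sided |
|---|---|---|
| 25 | 50.8% | 63.6% |
| 26 | 52.4% | 65.1% |

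The normal approximation gives 52.4% and 54.0% for the two-sided cases. The planned allowance is one patient in 26 per arm, or 3.8%. As an illustration only, since the article gives no attrition rate, 22 evaluable per arm would give 45.7%.

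**Step 5. What 25 per arm can detect.** The standardised effect detectable with 80% power is 0.809.
- At SD 14: 0.809 × 14 = **11.3 points**, which is 11.3/8 = 1.4 times the stated difference.
- For a difference of 8, the SD would have to be 8/0.809 = **9.9**.

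**Step 6. Sensitivity to the SD**, which the article gives only approximately (two-sided t test):

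| SD | Required per arm | Power at 25 per arm |
|---|---|---|
| 13 | 43 | 56.8% |
| 14 | 50 | 50.8% |
| 15 | 57 | 45.5% |

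**Step 7. Expected precision.** The 95% CI half-width is t(48) × 14 × √(2/25) = 7.96 points. An estimate of exactly zero would exclude 8 by only 0.04 of a point. Almost any estimate in favour of the block would leave 8 inside the interval.

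**The case against.** The strongest objection concerns the assumptions behind the headline figures. The article does not state sidedness, and its hypothesis is directional. Under a one-sided test, 25 is about 64% of the 39 required, not half, and power is 63.6%, not 51%. The SD is also approximate, so a single power figure suggests more precision than the input supports. Both points stand as qualifications, and the ranges are shown for that reason. Neither rescues the claim of 80%: two-sided is the ordinary reading, a one-sided test still falls well short, and 25 per arm would need an SD near 10, which does not fit a value described as about 14.

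It can also be said that 50 and 52 do not truly conflict, because the sample size section separates the number required from the number to recruit. That is a fair reading. The abstract and Background can be taken as quoting the required number, so this is a matter of clarity. Likewise, with an outcome at 24 hours, an allowance of 3.8% is not clearly too small, although the Recruitment section also says that data affected by a protocol breach will not be analysed, which could remove further patients.

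Lastly, a rule for reading a non-significant result often belongs in an analysis plan that is not shown here. That bears on where the rule is written. The error in the stated power remains.

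**Conclusion.** The concern holds. From the article's own inputs, the required size is 49 to 50 per arm and not 25. Power at the stated size is about 51%, and 80% power exists only for a difference of about 11.3 points. These figures assume a two-sided 5% test, equal arms, an unpaired t test and SD 14. Over SD 13 to 15, two-sided power at 25 per arm runs from about 57% to 46%; a one-sided test at SD 14 gives about 64%. No combination within those ranges supports the statement as written, and the Mann-Whitney alternative would, for normally distributed data, need slightly more patients. Because the claim concerns the primary outcome and will be quoted when the result is interpreted, it must be corrected.

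**What to change.** 1. Correct the sample size section to say that, with a two-sided 5% unpaired t test and SD 14, 25 per arm gives about 51% power for 8 points, or 80% power for 11.3 points. State the sidedness.
2. If 80% power for 8 points is to be kept, give the requirement as 50 evaluable patients per arm, before any allowance for withdrawals.
3. Use one enrolment target (50 or 52) in the Abstract, the Background and the sample size section, or label each figure as required or recruited.
4. State, here or in the analysis plan, that a non-significant primary result will be read from the 95% confidence interval against 8 points and not as absence of benefit.

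Items 1, 3 and 4 change wording only. They cost a less favourable stated power and no patients, and they remain worth making if recruitment has finished. Item 2 would about double the trial. The Trial status section reports 4 patients enrolled by 11 May 2020 and completion expected by 31 January 2021, so whether it is still feasible is for the sponsor to say.

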### Patient and public involvement

A patient information leaflet was written in “plain English” for trial participants. This was written in collaboration with and approved by our patient representative group. On the advice of the same group, we chose the QoR-15 questionnaire as opposed to the QoR-40 as the former was deemed to be easier for patients to read and comprehend. We also consulted with our patient advisory group on the drafting of our consent form. On their advice, we included a statement to say that their data protection rights would not be affected by participating in the study (Fig. 2).

**Fig. 2 Fig2:**
[figure not shown]
Study flow chart outlining time scale of enrolment, intervention and assessment

## Discussion

We are conducting this multicentre, randomised control trial to investigate the efficacy of ESP in thoraco-lumbar spine surgery in terms of quality of recovery. The ESP block has become increasingly popular in recent times, and its use has been reported in a range of thoracic and abdominal surgery [18–20]. Its use in spinal surgery is less well documented and existing trials have used the traditional end points of opioid consumption and pain scores to assess its efficacy [7, 10, 21]. To the best of our knowledge, no trial to date has examined the impact of the ESP block on quality of recovery in spine patients.

Spine surgery is associated with significant postoperative pain and often a protracted recovery period. Current evidence suggests that the implementation of Enhanced Recovery After Surgery (ERAS) programmes in spine surgery may lead to improvements in functional recovery, length of stay, opioid use, complications and readmissions [22]. Because of its reputed analgesic benefits, ESP block may have a role as part of an ERAS programme and merits further investigation. By blocking the posterior rami of the spinal nerves, many structures traumatised during posterior approach spinal surgery could be targeted for alleviation by an ESP block.

More than 70% of patients presenting for major spinal surgery will already be taking opioids for pain relief. Preoperative opioid use combined with poorly controlled pain scores postoperatively have been identified as risk factors associated with opioid misuse during the postoperative period [23]. Given current public health concerns regarding addiction to prescription opioids administered postoperatively, particularly in the USA, there is a real need to focus our attention towards non-opioid based adjunctive analgesic strategies. Although ESP is a new regional anaesthetic technique, a recent meta-analysis provides moderate-quality evidence that the ESP block can reduce postoperative pain scores and opioid requirements after a range of surgeries [24]. The ESP block provides an exciting opportunity for investigators to possibly make a meaningful impact in patient-centred postoperative outcomes for spine surgery patients.

This protocol will result in the attending anaesthesiologist not being blinded to the group allocation as they will be required to perform the block. This is as an unavoidable situation, as for safety reasons will we feel that the treating anaesthesiologist should be aware that their patient has received 40 ml of 0.25% levobupivacaine. However, the primary outcome is the QoR-15 score at 24 h postoperatively which will be assessed by study members blinded to the group allocation.

We have chosen to exclude patients requiring surgical intervention of five or more vertebral levels. The rational for this decision comes from cadaveric studies, which suggest the maximum spread of local anaesthetic from a single injection ESP block to be approximately 5 levels [25]. Therefore, surgical dissection beyond this point is unlikely to benefit from a single shot technique, as proposed in this trial.

Pain scores and quality of recovery will be recorded up to 24 h postoperatively. We acknowledge that for many patients having major spinal surgery their recovery will continue beyond this point. We believe that any analgesic benefit derived from a single dose of local anaesthesia is unlikely to persist beyond 24 h, and so we will not assess pain scores after this point. However, length of stay and postoperative complications will continue to be monitored after this period.

ESP blocks will be done under general anaesthesia, therefore formal dermatomal assessment of block function will not be performed. This raises the possibility that some blocks may not be fully effective. However, the practice of administering these blocks under ultrasound guidance after induction of general anaesthesia is consistent with routine clinical practice, and therefore our findings should still be applicable to widespread clinical practice.

We do not intend to assess patients’ preoperative QoR-15 in this study. Consequently, we will not have a baseline from which to compare postoperative scores and this we accept is a limitation of the study. Nonetheless, QoR-15 was designed for postoperative use, and we will apply this tool to both randomised cohorts equally. Further, the ability of QoR-15 in the immediate preoperative period to give an accurate baseline has been questioned [26].

Recovery from spinal surgery can be an arduous journey for our patients. By employing a patient-centred focus to our trial design, we hope to evaluate whether this relatively straightforward regional anaesthetic intervention can facilitate recovery and improve safety for patients by reducing postoperative morbidity and complications. This trial is designed to answer that question.

### Trial status

As of May 11, 2020, 4 patients have been enrolled in this trial. Recruitment began on 1 May 2020 and is expected to be completed by 31 January 2021. This is protocol version 1 dated 3 April 2020.

## Data Availability

Data will be available upon reasonable request.

## Abbreviations

AUC: Area under the curve
CCI: Comprehensive Complication Index
ERAS: Enhanced Recovery After Surgery
ESP: Erector spinae plane
LOS: Length of in hospital stay
PACU: Post anaesthesia care unit
QoR-15: Quality of Recovery-15 item questionnaire
VRS: Verbal response scale
